### Sample size

The group-based intervention will include six children per group, with a total of three groups planned. We aim to include at least 18 children. This sample will allow description of response patterns at the individual level as well as analyses at the group level. Repeated measurements across study phases will make it possible to examine changes over time within participants and across the cohort, thereby strengthening the robustness and generalizability of the conclusions regarding intervention effectiveness.

### Training protocol

#### Preparation for the FSA program

The intervention consists of a 12-week combined training programme comprising daily parent-delivered home-based goal-directed training and Frame Running, in addition to a 90-minute group training session held once weekly at Astrid Lindgren Children’s Hospital and supervised by experienced physiotherapists and occupational therapists.

#### Frame runners

Each child will receive their own Frame Runner to be used both at home and during group training. A Frame Runner is a three-wheeled running frame designed to support people with physical disabilities. It has two wheels in the back and one in the front, a saddle that supports the body weight of the user without restricting leg movement, and handlebars that help with steering and stability. The chest plate offers help with stability, and the trunk can be secured with straps if needed. The Frame Runner has no pedals, instead, users propel themselves by running or walking with their feet on the ground, or by using a “leg-swing” pattern in which both legs push off simultaneously. It is available in different sizes and can be used by children as well as adults, allowing them to move independently and at higher speeds than they typically can without support.

At the first baseline assessment, each child will be fitted with a Frame Runner to ensure the correct size, height and proper adjustments. Each child will receive one individually fitted Frame Runner, which they will keep and use throughout the study. The Frame Runner will be stored at the hospital during the baseline phase but will be taken home at the start of the training phase and throughout the training period. Further adjustments will be made when needed. This session will also provide time to become familiar with the Frame Runner and acquire basic experience.

#### Goal setting procedure

The initial goal-setting discussion will start at the second baseline assessment, where the concept of goals will be introduced. This discussion will occur after administration the PEDI-CAT mobility dimension, which helps identify each child’s current functional abilities and highlights areas for further development. The aims should be activity-based and related to mobility (e.g., sit-to-stand, walking, jumping and Frame Running). Families will be actively involved throughout the process, beginning with an exploration of the child’s interests. The discussion will focus on meaningful, realistic activities in the child’s daily environment that can be integrated into daily routines to support intensity of training. Parents will be encouraged to go home and reflect on the potential goals or alternative goals that are realistic and attainable within a three-month period. At the third baseline assessment, two to three individualized goals will be discussed and finalized for each child. The procedure will include describing baseline performance and specifying intermediate steps leading toward achieving the final goals. Goals achievement will be carefully aligned with each child’s current level, ensuring that they are challenging yet attainable. The scaling will be reviewed with the PIs to ensure one-dimensionality.

Once the goal is finalized, the family and the therapist will discuss strategies for integrating them into daily routines. For each goal, a Goal Attainment Scaling (GAS) will be applied, specifying the present level, the expected level of performance and criteria for exceeding expectation (see assessments). A completed form will be provided for the family. Each specific goal will also be recorded by the families in the child’s daily environment.

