#### Home training

Parents will be encouraged to continue daily practice at home using the Frame runner and activities aligned with their child’s goals, to promote repetition and consolidation. Treatment planning will be undertaken in collaboration with the family and will be guided by the GAS goals, with a focus on progressing to the next step. The plan will be reviewed with the therapist prior to the start of training and on a weekly basis; during each group training session, time will be allocated for families to discuss progress and any need for adjustments. The amount of training completed will be recorded in a weekly diary by parents.

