### Accelerometer set-up and analysis

The SENS Motion system is a thigh-worn accelerometer measuring 3-axis acceleration. Accelerometry data will be collected at five different time points during the study period (Tables 2 and 1). The raw acceleration data will be compared between time points as a measure of total activity and time presented as non-sedentary activity (minutes). Data will also be analyzed based on individual cut-off values (percentages of max acceleration during 30 m Frame Running sprint) and presented as minutes/day in different intensity zones. Accelerometers will be attached with adhesive tape to the outer thigh of the dominant/least affected leg. They will be worn for seven consecutive days, including an entire weekend. In a diary, parents note any unusual physical activity or inactivity, such as bed rest due to illness, to inform subsequent data analysis.

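### The B3 accelerometry week, one of only two baseline activity weeks, may be worn after goals and home strategies have been settled with the family

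*Protocol article*

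**What the plan says.** The Goal setting procedure spreads goal setting over two baseline visits. At B2: "The initial goal-setting discussion will start at the second baseline assessment, where the concept of goals will be introduced". This comes after the parent interview: "This discussion will occur after administration the PEDI-CAT mobility dimension". Between the visits, "Parents will be encouraged to go home and reflect on the potential goals or alternative goals". Then "At the third baseline assessment, two to three individualized goals will be discussed and finalized for each child", followed by "Once the goal is finalized, the family and the therapist will discuss strategies for integrating them into daily routines". The same section provides for a completed form for the family and for recordings of each goal made by the family. It does not date the strategy talk, the form or the recordings more closely, and it gives no order of testing and goal talk at B3.

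The other programme component is held back explicitly, under Frame runners: "The Frame Runner will be stored at the hospital during the baseline phase". On the home plan, Home training says: "The plan will be reviewed with the therapist prior to the start of training and on a weekly basis".

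Table 1 schedules accelerometry at B1, B3, F1 and F3, and Table 2 adds week 6. On wear, the accelerometer section says: "They will be worn for seven consecutive days, including an entire weekend". It does not say whether the seven days begin or end at the visit.

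**The concern.** A baseline week should show the child's activity before the programme reaches the family. Parents are the main trainers in this programme, and the section on its framework expects training intensity to come from building practice into everyday routines. A family that leaves B3 with settled goals, strategies for daily routines and a form can begin at once. No equipment or session is needed, and nothing in the text asks them to wait.

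The measure exposed is accelerometry, which serves the secondary objective of raising overall physical activity. It has only two baseline weeks. If one of them already contains practice, the baseline is too high, the change to follow-up looks too small, and the step from B1 to B3 looks like a rise before training. The individual-level analysis inspects level and trend, so such a step could be misread.

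**Working it through.** **Schedule.** Table 1 gives four accelerometry time points (B1, B3, F1, F3) and Table 2 gives one (week 6): 4 + 1 = 5. This matches the five stated in the accelerometer section. Two of the five, B1 and B3, lie before training, so B3 is half of the activity baseline.

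**Where the B3 week can fall.**
- Worn from the B3 visit onward: 7 of 7 days follow goal finalisation, and they may follow the strategy talk and the form.
- Worn up to the B3 visit: 0 of 7 days do.

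The text does not choose between these, but two features point to the first. B1 is the first baseline assessment, so its wear week most naturally starts there, and the same routine would carry over to B3. The intensity zones are scaled to acceleration in the 30 m Frame Running sprint, a visit test, so the sensor is presumably on the child at a visit.

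**Effect on the activity change.** Let D be the true change from untrained baseline to follow-up, and c the share of D already present in the B3 week. Assume no other change between B1 and B3.
- B1 alone as baseline: observed change = D
- B3 alone: D − cD = D(1 − c)
- Mean of B1 and B3: D − (0 + cD)/2 = D(1 − c/2)

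The documents give no c, and Statistical method does not say which baseline value enters the comparison. The values of c below are therefore assumptions, with 0.50 as an outer bound. The power figures are also only an illustration: paired t-test, n = 18, two-sided 5%, and a standardised change of 0.70 when c = 0 (noncentrality 0.70 × √18 ≈ 2.97, power 80%). The standard deviation of the change is held equal across baseline choices. The protocol states no power, effect size or significance level.

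| c (assumed) | B3 alone: change kept | Power | Mean of B1 and B3: change kept | Power |
|---|---|---|---|---|
| 0 | 100% | 80% | 100% | 80% |
| 0.10 | 90% | 71% | 95% | 76% |
| 0.25 | 75% | 56% | 87.5% | 69% |
| 0.50 | 50% | 29% | 75% | 56% |

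With B1 alone the change is kept in full for every c.

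**Other B3 measurements.** Clinic tests and parent interviews at B3 are taken at the visit. Whatever is done before the goal conversation cannot be affected by finalised goals, strategies or the form. Only the B2 introduction and the reflection at home come before it.

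**The case against.** The strongest reply is that the exposure is not established. The wear window and the interval from B3 to week 1 are not stated, and Fig. 1, the study timeline, could not be read here and may settle both. The strategy talk and the form carry no date. The scaling is also reviewed with the principal investigators, so the form may reach the family after the visit. Goal-directed home training is defined as part of the 12-week intervention, the diaries run only from week 1 to week 12, and nothing asks families to train during baseline. Any practice before week 1 would take place without the Frame Runner and without group sessions, so c may be small.

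All of this stands as a limit on certainty. It does not remove the point. The protocol guards one component against an early start and leaves the other unguarded, at a visit where a seven-day activity measurement is also scheduled.

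Two stronger readings are tempting, and the documents support neither:
- A reader might infer that all B3 values, including GMFM-66, are contaminated. Before the B3 visit families have only been introduced to goals and asked to reflect, with no practice requested. B3 tests are exposed to the finalised goals only if they are done after the goal conversation.
- A reader might extend the B1-to-B3 slope across the 12 training weeks as the expected course without training, and conclude that most of the gain would vanish. The protocol plans visual inspection and paired comparisons, not such an extrapolation.

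**Conclusion.** The concern holds in limited form. The schedule permits, and on its natural reading suggests, that the second baseline activity week follows goal finalisation. It does not say so outright. If it does follow, and if families begin to practise, the activity change is understated by c with B3 alone as baseline or by c/2 with the mean of B1 and B3. The size of c is unknown, and the direction rests on the assumption that practice raises measured activity.

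The bias is conservative: it would hide part of a real gain and would not create a false one. The B1 week comes before all goal setting and stays clean. The consequence is confined to accelerometry, unless B3 tests are done after the goal conversation. It is worth correcting because a change of measurement timing can avoid most of it.

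**What to change.** Change the timing of the measurement and leave the training as it is.

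1. Issue the sensor at or after B2 and state that the B3 wear week ends at the B3 visit. If the child keeps it on until the 30 m sprint, that visit can still supply the sprint reference.
2. State that all B3 tests and interviews are completed before the goal conversation at that visit.
3. Add one sensitivity analysis of the accelerometry outcomes with B1 alone as baseline. It is free of this bias but rests on a single week, so it should accompany the main comparison and not replace it.

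The cost is a few lines of scheduling text and one extra analysis, with no added visit, child or staff. There are small downsides. The sensor has to reach the family before B3, and the B2-to-B3 interval, which the article does not give, must hold seven days with a full weekend. The moved week would still follow the B2 introduction of goals, a weaker exposure that the B1-only analysis covers.

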### Procedure for weekly group training

The weekly group training session, lasting 90 min, will be conducted at Astrid Lindgren Children’s Hospital, Stockholm, Sweden. The intervention will take place in an open indoor facility divided into two areas: one for Frame Running and one for goal directed gross-motor training. A team of one occupational therapist and three physiotherapists will lead the sessions. The therapists responsible for group-based activity training are all very experienced in pediatrics, with a special interest in intensive training and physical activities. Parents act as the primary trainers for their child while therapists will facilitate and coach, supporting parents as a guide for their child through the activities.

The training session will begin with a short group gathering designed to establish routine, engagement and connection. This will include a welcome song, introduction of children, parents and therapists as well as relevant information. The children will then be divided into two subgroups: one will start with 30 min of Frame Running, and the other with 30 min of goal directed gross-motor training. During both activity sessions, heart rate will be monitored using heart-rate monitors on the upper arm. All children, parents and therapists will come together during a 15-minute break for social interaction and a healthy snack to keep energy balance. After the break, the groups will switch activities. At the end of the session, all participants will reconvene to sum up the day.

#### Goal directed gross-motor training

Each session will include six to eight activity stations, tailored to the children´s ability and different goals. Each child`s goals will be displayed on the wall to make it easy for both therapists and families to remember the focus. The area will be equipped with materials such as mats, benches, trampolines, a small basketball hoop, a play kitchen, inviting toys and materials that arouse curiosity and promote interaction. Activities will address gross motor activities such as standing up, walking, turning, jumping, stairclimbing, or navigating short obstacle paths. Since the program is highly individualised, there will be specific instruction for each child on each station to support the child’s individually tailored training. The setup will aim to encourage high repetition practice and self-initiated movement through play. The therapists will provide guidance by modeling appropriate exercise techniques, offering feedback, and ensuring that the level of challenge is adjusted to the child’s individual capabilities and specific goals.

### The frame running training

To promote moderate- to high-intensity exercise, related to ability level and age, the room will be arranged with a straight track of 20 m allowing for variations in speed, duration and turning, while maintaining safety and motivation. Training will be individualized and tailored to each child’s abilities. Exercise intensity will be promoted through motivational, playful, game-based activities delivered by highly experienced therapists. These may include tag-style games with parents or therapists, searching for hidden objects, or collecting points. The space will feature thematic decorations and music to sustain engagement. Themes tailored to individual interests can be added to further enhance enjoyment and participation. All games will be structured to prompt spontaneous bursts of running, rapid directional changes, and acceleration. Specific adaptations to support participation across a range of abilities may include visual aids (e.g., color-coded pathways for children with visual impairments), acoustic adjustments for those with sound sensitivity, and additional verbal or visual cues to enhance comprehension and task execution. The aim is to achieve the highest possible intensity during the 30-minutes training session which will be monitored using heart rate monitoring.

#### Home training

Parents will be encouraged to continue daily practice at home using the Frame runner and activities aligned with their child’s goals, to promote repetition and consolidation. Treatment planning will be undertaken in collaboration with the family and will be guided by the GAS goals, with a focus on progressing to the next step. The plan will be reviewed with the therapist prior to the start of training and on a weekly basis; during each group training session, time will be allocated for families to discuss progress and any need for adjustments. The amount of training completed will be recorded in a weekly diary by parents.

#### Study protocol

Data collection will take place at the Astrid Lindgren Children’s hospital and at home according to the schedule shown in Tables 1 and 2; Fig. 1. The assessment takes about 1,5 h and the Gait analysis takes additional 1,5 h.

**Table 2 Tab2:** Assessment to be collected at the different time points during the study, W = Week

Assessment	W 1	W 2	W3	W4	W5	W6	W7	W 8	W9	W10	W11	W 12
Prime SP	X			X				X				X
Accelerometry						X						
Heart rate	X	X	X	X	X	X	X	X	X	X	X	X
Diary	X	X	X	X	X	X	X	X	X	X	X	X

##### Quality assurance

Project organization will be managed by the PIs (ACE and FvW) and the study coordinator (AA). Data collection will be performed by a team of investigators, all previously experienced in collecting data from the actual assessments and not involved in the training session. Regular reviews of project progress and quality checks and quality assurance of all uploaded data will take place regularly on all data uploaded to the digital platform REDCap by one of the PIs (ACE) also responsible for exporting data when there is time for analysing data.

### Procedure for data collection

Data collection will take place during a two-hour session at the Astrid Lindgren Children´s hospital and gait analysis will take place on a separate occasion at the Motion analysis laboratory at Astrid Lindgren Children’s Hospital, Stockholm, Sweden. Additional data collection will occur during the intervention period via weekly logbooks and questionnaires regarding the children’s engagement in training, completed through REDCap. Physical activity intensity will also be measured using accelerometry and heart rate monitoring during the training sessions and at home. The complete assessment battery and timing across all study phases are summarized in Table 2. The assessment battery was selected to address the aims of the study as well as the hypothesis. The data collection will be administrated by the study coordinator (AA). The assessors have good knowledge and experience of performing the assessments in the clinic and for research. The observational assessments will be performed by an experienced pediatric physiotherapist (EH). Skeletal muscle morphology assessments (ultrasound) will be conducted by an expert in musculoskeletal imaging (MA) and a pediatric radiologist (OK). Activity monitoring and physiological measurements during the intervention (accelerometry, heart rate monitoring) will be supervised by a medical doctor (JS) and an exercise physiologist (JN). Gait analysis will be performed at the Motion analysis laboratory by a team of lab staff and clinicians (CL, AE, KA). The study coordinator (AA) will collect questionaries and support parents to formulate individually tailored goals for each child prior to the start of the intervention. Weekly home-based training diaries and engagement questionnaires will be completed in REDCap by parents throughout the intervention period (Table 1). The different assessments that will be used and at what time points data will be collected are described in Table 1.

### Primary outcome measure

#### Gross motor capacity

*Gross Motor Function Measure (GMFM-66)*, is an observational, standardized and criterion-referenced measure, developed to evaluate change in gross motor function in children with cerebral palsy [45]. The 66 items cover gross motor capacity from lying and rolling, to walking, running and jumping. Item scores (0–3) are converted to an interval score from 0 (low capacity) to 100 (high capacity) (Rasch analysis), where typically developing five-year-olds are expected to achieve a score of 100. GMFM-66 is reported to be valid, reliable and responsive to changes in gross motor capacity in children with CP [46]. In addition, the subscales “D. Standing and E. Walking and Jumping will be used from GMFM-88 [47]. The assessments will be performed barefoot and video-recorded to allow verification of scoring and reliability check if needed. To assess inter-rater reliability and strengthen the internal validity of the study, a subset of the GMFM recordings will undergo blinded secondary scoring (see statistics).

### Accelerometer set-up and analysis

The SENS Motion system is a thigh-worn accelerometer measuring 3-axis acceleration. Accelerometry data will be collected at five different time points during the study period (Tables 2 and 1). The raw acceleration data will be compared between time points as a measure of total activity and time presented as non-sedentary activity (minutes). Data will also be analyzed based on individual cut-off values (percentages of max acceleration during 30 m Frame Running sprint) and presented as minutes/day in different intensity zones. Accelerometers will be attached with adhesive tape to the outer thigh of the dominant/least affected leg. They will be worn for seven consecutive days, including an entire weekend. In a diary, parents note any unusual physical activity or inactivity, such as bed rest due to illness, to inform subsequent data analysis.

### Secondary outcomes

#### Classifications and standardized assessments

*The Gross Motor Function Classification System – Expanded and revised (GMFCS-ER) and the Manual Ability Classification System (MACS)* are five-level classification systems describing gross motor function and manual ability in children with CP. The appropriate level is determined after discussions with caregivers and therapists who are familiar with the definitions of each level [48, 49].

*Pediatric Evaluation of the Disability Inventory (PEDI-cat)* is a norm and criterion-referenced questionnaire which evaluates the child’s daily performance and need of caregiver assistance. In this study we will use the long version of mobility [50]. A structured interview with the parents will be conducted to obtain information about the child’s performance in the daily environment. The summary scores can be converted to normative standard scores and scaled scores. The normative scores are available for children 6 month to 7.5 years. The scaled scores range on a continuum from 0 to 100. PEDI is available in a Swedish version [51].

*Functional Mobility Scale (FMS)* describes mobility performance across three distances − 5 m, 50 m, 500 m, and the child’s use of assistive devices, in daily life. It determines the level of independence and need for assistive devices [52]. The assessment is based on a brief interview rather than direct observation. The clinician asks how the child usually moves around short distances indoors (5 m, e.g., at home), medium distances (50 m e.g., in and between rooms at preschool), and long distances (500 m, e.g., in a shopping center). Ratings reflect what the child does (performance), not capacity.

